## Abstract

**Background:**

The COVID-19 pandemic has brought attention to the importance of correctly using personal protective equipment (PPE). Doffing is a critical phase that increases the risk of contamination of health care workers. Although a gamified electronic learning (e-learning) module has been shown to increase the adequate choice of PPE among prehospital personnel, it failed to enhance knowledge regarding donning and doffing sequences. Adding other training modalities such as face-to-face training to these e-learning tools is therefore necessary to increase prehospital staff proficiency and thus help reduce the risk of contamination.

**Objective:**

The aim of this study is to assess the impact of the Peyton 4-step approach in addition to a gamified e-learning module for teaching the PPE doffing sequence to first-year paramedic students.

**Methods:**

Participants will first follow a gamified e-learning module before being randomized into one of two groups. In the control group, participants will be asked to perform a PPE doffing sequence, which will be video-recorded to allow for subsequent assessment. In the experimental group, participants will first undergo face-to-face training performed by third-year students using the Peyton 4-step approach before performing the doffing sequence themselves, which will also be video-recorded. All participants will then be asked to reconstruct the doffing sequence on an online platform. The recorded sequences will be assessed independently by two investigators: a prehospital emergency medicine expert and an infection prevention and control specialist. The assessors will be blinded to group allocation. Four to eight weeks after this first intervention, all participants will be asked to record the doffing sequence once again for a subsequent skill retention assessment and to reconstruct the sequence on the same online platform to assess knowledge retention. Finally, participants belonging to the control group will follow face-to-face training.

**Results:**

The study protocol has been presented to the regional ethics committee (Req-2020-01340), which issued a declaration of no objection as such projects do not fall within the scope of the Swiss federal law on human research. Study sessions were performed in January and February 2021 in Geneva, and will be performed in April and June 2021 in Bern.

**Conclusions:**

This study should help to determine whether face-to-face training using the Peyton 4-step approach improves the application and knowledge retention of a complex procedure when combined with an e-learning module.

**International Registered Report Identifier (IRRID):**

PRR1-10.2196/26927

## Introduction

### Background and Importance

The emergence of COVID-19 has democratized the use of personal protective equipment (PPE) for all health care workers in and outside hospitals [1] in accordance with international recommendations [2]. Donning and doffing procedures contribute to the adequate use of PPE and reduce the risk of self-contamination of caregivers [3]. This last point is critical as frontline health care workers are a scarce and essential resource who are at increased risk of being contaminated [4].

Although the donning phase is associated with a low risk of contamination, doffing is a critical phase and greatly increases the risk of contamination of caregivers [5-9]. One of the strategies that effectively contributes to reducing staff self-contamination is doffing in structured areas dedicated to the removal of PPE [10,11]. However, this strategy is difficult to apply in the prehospital field, where health care workers must often doff PPE on site. It is therefore all the more relevant to train prehospital health care workers in the noncontaminating removal of PPE so that they can perform it adequately under all circumstances*.*

Two previous studies have shown that training prehospital staff in using PPE through a gamified electronic learning (e-learning) module increases the proportion of making an adequate choice of PPE [12,13]. However, this module failed to improve knowledge acquisition of correct doffing sequences. It was therefore concluded that e-learning training alone is insufficient to adequately train prehospital staff in the noncontaminating removal of PPE, and that other training modalities should be considered, either as standalone interventions or in combination with this module. The Peyton 4-step teaching approach [14] is an effective training structure that has been shown to increase knowledge and skill retention when compared to standard training in the acquisition of procedural skills [15]. Our hypothesis is that adding a face-to-face training modality using the Peyton 4-step approach to a gamified e-learning module could increase the proficiency of prehospital workers regarding this procedure, thus reducing the risk of contamination of prehospital staff [16].

### Objectives

The primary aim of this study is to define whether the Peyton 4-step approach used in addition to our gamified e-learning module for teaching noncontaminant PPE removal increases the percentage of correct PPE doffing sequences performed by first-year paramedic students in comparison to e-learning alone.

## Methods

### Study Design and Setting

We will carry out a parallel-group, randomized, quadruple-blind (participants, instructors, outcome assessors, and data analyst) controlled superiority trial designed following the SPIRIT statement (see Multimedia Appendix 1 for the SPIRIT Checklist) [17], and including relevant elements from the CONSORT-EHEALTH checklist [18] and from the CHERRIES guidelines [19]. The design is detailed in Figure 1.

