### Enrollment and Consent

Prior to the beginning of the study, students will be sent emails containing general information about the study (Multimedia Appendix 4). The home screen of the website will contain information regarding the study, including data security and the learning objectives (Figure 2 and Figure 3). Consent (including for the recording of videos) will be gathered electronically. Participants will be informed that they will attend, during the course of their learning path, a workshop on correct PPE doffing according to good practices validated by IPC experts.

Participation will be free and each participant will be able to withdraw at any time without giving any justification. Participants will benefit from this study by acquiring knowledge regarding the safe doffing of PPE, which will be useful in their practice. There will be no financial compensation or incentive.

The data collected are encoded using the randomly assigned connection identifiers; thus, if a participant keeps their identifiers, it will be possible for them to request that the answers be deleted once the survey is completed.

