### Study Sequence

After picking up an envelope, each participant will be asked to log into the platform with specific credentials. The welcome screen will be the same for both groups and, similar to the envelopes, will not contain any information regarding the study sequence to ensure that participants are adequately blinded.

After clicking the start button, a first questionnaire designed to collect demographic data will be displayed (Multimedia Appendix 5). Learning preferences (visual, aural, reading/writing, or kinesthetic [VARK]) will be assessed using the online VARK questionnaire, which will be displayed in the student’s preferred idiom (either the French version translated by [name] [29] or the German version translated by [name] [30]), with permission from the original author ([name]). This questionnaire consists of 16 multiple-choice items with four response options; possible scores range from 0 to 16 for each subscale. The VARK questionnaire has shown adequate validity and reliability [31]. Participants will access the VARK questionnaire by clicking on a link displayed on the online platform at the end of the first questionnaire; the results will be reported on a paper case report form (CRF; Multimedia Appendix 6) by one of the investigators before being entered directly on the study platform; a double check by the participant countersigning the document will be used to limit potential copy errors.

Both groups will then follow the e-learning module, the development of which has previously been described [32]. This module was initially developed in French and will be translated in German for the purpose of the study.

After completing the module, participants belonging to the control group will be asked to don the following PPE: protective glasses, FFP2 mask, coverall with hood, and gloves. They will then be asked to perform the doffing sequence individually, which will be recorded on video. After completing the doffing sequence, participants will be asked to go back to the online platform to electronically rebuild the doffing sequence.

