Rather than immediately donning and doffing the PPE after completing the e-learning module, participants in the experimental group will be randomly allocated to the instructors to follow face-to-face learning according to the Peyton 4-step approach. After completing this workshop, these participants will resume the same path as their counterparts from the control group by moving on to the video recording of the doffing sequence and, finally, by being asked to rebuild the doffing sequence on the online platform.

Four to eight weeks later, depending on the schools’ schedules, participants will be asked to take part in a second session. This time interval is sufficient to reliably assess retention, which has been shown to be nonlinear. Out of the proportion of participants who display a significant decline in knowledge retention at 3 months, half will already present a significant decline in knowledge retention after 4 weeks [33]. Both groups will first repeat the video recording of the PPE doffing sequence and then reconnect to the platform to reconstruct the doffing sequence by computer. The experimental group will then be considered as having completed the study path, while the control group will attend a face-to-face learning session (See SPIRIT diagram in Multimedia Appendix 7 and Figure 1).

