### Secondary Outcomes

Seven secondary outcomes will be assessed: time required to teach the technique, time required to perform the doffing procedure, learner satisfaction, proportion of correct computer sequences, confidence in using PPE, and knowledge and skill retention.

The time required to teach the technique using the Peyton approach will be recorded on a paper CRF (Multimedia Appendix 9) by the instructor. Time will be measured from the beginning of step 1 until the last participant has completed the fourth and final step.

The time required to perform the doffing sequence will be recorded (in seconds) by analyzing the recording (measured from the moment the first item is taken off until the moment the learner announces that the procedure has been completed).

Learner satisfaction will be measured using a 5-point Likert scale (not satisfied at all, not satisfied, neutral/undetermined, satisfied, very satisfied).

Computerized doffing sequence accuracy involves reordering the presented sequence in random order in two steps: first in the contaminated zone and then in the noncontaminated zone.

Confidence in the ability to use PPE will also be assessed using a 5-point Likert scale (not confident at all, not confident, neutral/undetermined, confident, very confident).

Knowledge retention will be assessed by reordering the computer sequence once again 4-8 weeks after the first acquisition intervention, whereas skill retention will be assessed in the same way as the primary outcome.

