### Blinded Data Collection and Assessment

Some outcomes will be recorded electronically. This will allow for their assessment to be independent from subjective human evaluation. For all other outcomes, assessors will be blinded to participant allocation.

Electronic data will be recorded and securely stored in an encrypted MariaDB database (Version 5.5.5; MariaDB Foundation) hosted on a Swiss server.

At the end of the study, all electronic data will be extracted to a comma-separated value file by the only investigator who will have access to the dataset ([name]). No personal data (name, first name, date of birth, or IP address) will be collected.

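### Participants know whether they had the workshop before they are filmed, so the participant part of the quadruple-blind label is wrong, and satisfaction and confidence are unblinded self-ratings

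*Protocol article*

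**What the plan says.** Study Design and Setting describes a "randomized, quadruple-blind (participants, instructors, outcome assessors, and data analyst) controlled superiority trial". For participants, the mechanism is given in Study Sequence: the envelopes and the welcome screen "will not contain any information regarding the study sequence to ensure that participants are adequately blinded". Enrollment and Consent adds that "Participants will be informed that they will attend, during the course of their learning path, a workshop on correct PPE doffing"; the timing of that workshop is not disclosed.

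The two paths separate after the e-learning module (Study Sequence). For controls: "After completing the module, participants belonging to the control group will be asked to don the following PPE", followed directly by the filmed doffing. In the other arm, "participants in the experimental group will be randomly allocated to the instructors to follow face-to-face learning", and filming comes afterwards.

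Blinded Data Collection and Assessment says of the outcomes captured by computer: "This will allow for their assessment to be independent from subjective human evaluation. For all other outcomes, assessors will be blinded to participant allocation". Secondary Outcomes measures learner satisfaction and confidence in using PPE on 5-point Likert scales. Statistical Analysis dichotomizes both for testing, with significance at P<.05.

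**The concern.** Participants are the first of the four parties listed as blinded, yet the intervention is a visible, attended training session that one arm receives before the outcome is recorded and the other does not. Concealing the path up to the split is useful: it protects allocation and avoids announcing who is a control. It does not make a participant blind to the treatment at the moment of measurement.

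Two things are at stake. First, blinding the video assessors protects the scoring of the doffing sequence, but not the filmed behaviour itself. Someone who knows that the announced workshop has not yet happened may approach the recording differently from someone who has just completed it. Second, self-ratings have no separate assessor to blind. A significant difference in satisfaction or confidence would be published as a result of a quadruple-blind trial, with more apparent protection from response bias than the design gives.

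**Working it through.** The plan gives no figure on this point and none is needed. The check follows what each party knows at each measurement.

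1. **Before the split (session 1, up to the end of e-learning).** The envelope, welcome screen, demographic questionnaire, VARK questionnaire and e-learning module are common to both arms. Participants know that a workshop will come at some time. They do not know their arm. The blinding claim holds here.

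2. **After the split, before the primary recording.** Controls put on the PPE and are filmed. Experimental participants attend the four-step face-to-face teaching and are then filmed. Combined with the advance notice of a workshop, a control knows at the camera that it has not taken place, and an experimental participant knows that it has. This applies to every participant who follows the assigned path, that is, up to all 62 students invited. What can remain hidden is the hypothesis, and which path counts as experimental.

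3. **Session 2.** Both arms are filmed and rebuild the sequence online before controls are trained. Each participant still knows whether the workshop has been received.

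4. **Who assesses each of the seven secondary outcomes.**
   - Doffing time and skill retention: taken from the recordings, under the blinded-assessor statement.
   - Computerized sequence at session 1 and knowledge retention: reordering tasks on the online platform, to which the statement about objective electronic recording can apply.
   - Teaching time: recorded by the instructor and defined only for the Peyton teaching, so there is no control-arm value to compare.
   - Satisfaction and confidence: rated by the participant.

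5. **Testing the blanket statement on those last two.** If the Likert items are captured electronically, the recording is automatic but the judgement is still a person's opinion, so the first half fails. If they count among the other outcomes, the assessor is the participant, who by step 2 knows what training was given, so the second half fails. Neither half can be true for these 2 of 7 outcomes.

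6. **Does the time of rating matter?** The article does not say when satisfaction and confidence are collected. Any rating made after the split comes from someone who knows the path followed so far. A rating made before the split could not reflect the intervention. The conclusion therefore does not depend on the missing time point.

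**The case against.** The strongest defence is that blinding here means unawareness of the design and hypothesis. With neutral wording about a workshop at some point, controls can suppose that theirs is simply still to come. That unawareness is real and worth reporting, but it is narrower than the unqualified claim in the design section. It may also be said that the statement on objective recording concerns only some outcomes and most naturally means the computerized sequence. That is a fair reading of its first sentence, but the next one covers all other outcomes and so takes in the two Likert items.

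It is also fair that lower effort or lower ratings among controls are possibilities, not facts shown in the text.

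A reader might infer more than the documents support:

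- *That the delayed control workshop is what reveals the arm.* It comes after the second recording and reconstruction: "The experimental group will then be considered as having completed the study path, while the control group will attend a face-to-face learning session". It cannot influence measurements already taken; the split in session 1 is the source of the knowledge.
- *That instructors are unblinded.* All their session 1 learners are experimental, and they might wonder on meeting other students at session 2. But Study Design and Setting says they are unaware that two training paths exist, and nothing shows that they learn otherwise.
- *That teaching time is a third compromised outcome.* It "will be recorded on a paper CRF (Multimedia Appendix 9) by the instructor", so the blinded-assessor wording fits it poorly. With no counterpart under e-learning alone, however, there is no between-arm contrast to bias.
- *That the participant information should be rewritten for Bern.* Spelling out that training may follow filming would disclose more of the sequence. It would also conflict with the commitments to leave the platform and the published protocol unchanged.

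**Conclusion.** The concern holds in limited form. The participant part of the quadruple-blind label is wrong as written, and the general statement on outcome assessment is false for two comparative secondary outcomes, satisfaction and confidence. This rests on the session 1 sequence being carried out as described and on participants having read the advance notice of a workshop. Even without that notice, each would know whether face-to-face teaching had been received.

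It would be a mistake to conclude that scoring of the primary outcome is unblinded. Two assessors rate the videos blind, receiving only recordings and codes built from login identifier and session number, and the analyst works with renamed groups. What remains open for the primary outcome is a performance or expectation effect in the filmed attempt, which the Limitations section does not mention. Its size cannot be derived from the documents. No sample size, test or estimate changes.

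**What to change.** - **Study Design and Setting, and the final report:** drop the quadruple-blind label. State that the video assessors and the data analyst are blinded to allocation, that instructors are unaware of the design, and that participants are unaware of the hypothesis but not of the training they received. The Abstract already claims blinding for the assessors only.
- **Blinded Data Collection and Assessment:** exempt satisfaction and confidence from the general statement, and report both as unblinded self-ratings that are supportive only.
- **Limitations:** add that blinding the assessors does not exclude performance or expectation effects in the filmed doffing.

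The Results section says the protocol will not be modified after publication. If that prevents a correction there, the report is the place to make it. The cost is a less favourable blinding label and less weight on two secondary results. Procedures, data collection and participant information stay as they are, so the change is still possible although the Geneva sessions are complete.

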### Online Platform

An online platform [26] running under the Joomla! 3.9 content management system (Open Source Matters) will be developed by [name] for the purpose of this study. A survey component (Community Surveys Pro 5.5 CoreJoomla) will be installed on the platform. [name] will be the only author to have access to the platform’s administration console. There will be no scheduled maintenance or update on the server during the study period. Once created, tested, and validated, the platform will not be altered before the end of the study period.

### Enrollment and Consent

Prior to the beginning of the study, students will be sent emails containing general information about the study (Multimedia Appendix 4). The home screen of the website will contain information regarding the study, including data security and the learning objectives (Figure 2 and Figure 3). Consent (including for the recording of videos) will be gathered electronically. Participants will be informed that they will attend, during the course of their learning path, a workshop on correct PPE doffing according to good practices validated by IPC experts.

Participation will be free and each participant will be able to withdraw at any time without giving any justification. Participants will benefit from this study by acquiring knowledge regarding the safe doffing of PPE, which will be useful in their practice. There will be no financial compensation or incentive.

The data collected are encoded using the randomly assigned connection identifiers; thus, if a participant keeps their identifiers, it will be possible for them to request that the answers be deleted once the survey is completed.

**Figure 2 figure2:**
[figure not shown]
French version of the platform welcome screen.

**Figure 3 figure3:**
[figure not shown]
German version of the platform welcome screen.

### Study Sequence

After picking up an envelope, each participant will be asked to log into the platform with specific credentials. The welcome screen will be the same for both groups and, similar to the envelopes, will not contain any information regarding the study sequence to ensure that participants are adequately blinded.

After clicking the start button, a first questionnaire designed to collect demographic data will be displayed (Multimedia Appendix 5). Learning preferences (visual, aural, reading/writing, or kinesthetic [VARK]) will be assessed using the online VARK questionnaire, which will be displayed in the student’s preferred idiom (either the French version translated by [name] [29] or the German version translated by [name] [30]), with permission from the original author ([name]). This questionnaire consists of 16 multiple-choice items with four response options; possible scores range from 0 to 16 for each subscale. The VARK questionnaire has shown adequate validity and reliability [31]. Participants will access the VARK questionnaire by clicking on a link displayed on the online platform at the end of the first questionnaire; the results will be reported on a paper case report form (CRF; Multimedia Appendix 6) by one of the investigators before being entered directly on the study platform; a double check by the participant countersigning the document will be used to limit potential copy errors.

Both groups will then follow the e-learning module, the development of which has previously been described [32]. This module was initially developed in French and will be translated in German for the purpose of the study.

After completing the module, participants belonging to the control group will be asked to don the following PPE: protective glasses, FFP2 mask, coverall with hood, and gloves. They will then be asked to perform the doffing sequence individually, which will be recorded on video. After completing the doffing sequence, participants will be asked to go back to the online platform to electronically rebuild the doffing sequence.

Rather than immediately donning and doffing the PPE after completing the e-learning module, participants in the experimental group will be randomly allocated to the instructors to follow face-to-face learning according to the Peyton 4-step approach. After completing this workshop, these participants will resume the same path as their counterparts from the control group by moving on to the video recording of the doffing sequence and, finally, by being asked to rebuild the doffing sequence on the online platform.

Four to eight weeks later, depending on the schools’ schedules, participants will be asked to take part in a second session. This time interval is sufficient to reliably assess retention, which has been shown to be nonlinear. Out of the proportion of participants who display a significant decline in knowledge retention at 3 months, half will already present a significant decline in knowledge retention after 4 weeks [33]. Both groups will first repeat the video recording of the PPE doffing sequence and then reconnect to the platform to reconstruct the doffing sequence by computer. The experimental group will then be considered as having completed the study path, while the control group will attend a face-to-face learning session (See SPIRIT diagram in Multimedia Appendix 7 and Figure 1).

